
#### ART interventions

All couples, either from the experimental arm or from the control arm, will benefit from a personalised follow-up in the context of usual fertility care, which includes:
A consultation with a physician specialist in reproductive biology who programs a standardised clinical and biological evaluation of infertility causesA multidisciplinary clinical and laboratory staff meeting leading to a decision of a therapeutic strategy, e.g., ovarian stimulation, intrauterine insemination (IUI), in vitro fertilisation (IVF)/intracytoplasmic sperm injection (ICSI).

This usual routine program actually will take at least 3 months and the first ART attempt will occur between three and 12 months since the initial visit (M0).

### Sample size and statistical analysis

We have considered (1) that the PEPCI intervention would lead to a relative risk of clinical pregnancy of 1.6 [28] as compared with usual care (i.e., from 20 to 32% in absolute values, respectively) and (2) that refusal of PEPCI experimental care would intervene for 20% of subjects. The resulting difference, according to the intention-to-treat principle, would therefore be 20% versus 29.6%. Given a two-sided alpha error of 5%, a power of 80%, and a randomisation ratio of 2:1 (control group:experimental group), 466 couples receiving usual care (control group) and 233 couples in the experimental group are required. The total sample size was set to 750 couples (500 control group and 250 experimental group participants), allowing room for a 5% dropout rate.

A flowchart will be used to depict the total participants of each cohort, those per group, and those per gender. All eligible participants will be included in the analyses (since they belong to the global observational cohort), and groups—that is, the randomised control group versus experimental group, encompassing couples having accepted PEPCI and couples having refused PEPCI—will be compared according to the intention-to-treat principle. General and baseline characteristics will be compared between the groups.

An analysis of the primary objective (i.e., the effect of intervention on clinical pregnancy) will be performed with a logistic regression mixed model, with a fixed factor corresponding to the randomisation-arm intervention group and the centre being considered as a random factor. The intervention group will be considered as superior if the lower-limit 95% CI of the corresponding OR of pregnancy is greater than 1. In addition, as a non-negligible proportion of couples may refuse to receive the intervention being trialled, the intention-to-treat analysis may, therefore, dilute any treatment effects. Thus, we will use the statistical method complier average causal-effect analysis, which provides unbiased estimates of the treatment effect for patients who comply with the protocol. This will be considered as a secondary analysis.

The analysis of the effect of the intervention on other criteria (e.g., adherence, satisfaction, BMI and diet, physical activity level, quality of oocytes and semen, fertilisation rate, pregnancy, occurrence of complications) will be performed by a generalised linear mixed-regression model; its link function and distribution of errors will be chosen according to the nature of the response.

No interim analysis will be performed.

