## Methods

### Experimental design

We propose a pragmatic randomised controlled multicentre trial of the improved effectiveness of an integrated global care program (PEPCI for Parcours Environnement PériConceptionnel en Infertilité) in comparison with usual care (i.e., a parallel-arm superiority trial). Four centres in Paris and its suburb area with various socioeconomic contexts will participate. Use of a pragmatic approach and an effectiveness assessment will assume not only clinical efficacy but also feasibility issues such as acceptability of care by patients under usual conditions as reflected by wide selection criteria [56]. Thus, this trial will use the ‘cohort multiple randomised controlled trial’ methodology [57] to strengthen external validity by limiting the bias that may result from the period of initial consent to randomisation or from the deception of being allocated to the control group.

Moreover, this design allows us to keep all people under survey to obtain realistic estimates of noncompliance and effectiveness of the program. It reproduces ‘patient-centred’ informed consent, in that the process of obtaining patient information and consent aims to replicate the one used in real-world routine health care.

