### Selection criteria

#### Whole cohort

Heterosexual infertile couples (lack of pregnancy after 12 months of unprotected intercourse), including men aged 18 to 60 years and women aged 18 to 43 years will be eligible for inclusion in the whole cohort. Other main inclusion criteria include a good understanding of the French language by both couple members and the approval of data collection by both parents-to-be.

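### The primary model adjusts for centre but not for female age, which randomisation does not balance either; prespecifying it would bring a modest gain in precision and robustness

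*Protocol article*

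**What the plan says.** Under *Sample size and statistical analysis*, the protocol article sets the primary model as a mixed logistic regression "with a fixed factor corresponding to the randomisation-arm intervention group and the centre being considered as a random factor". Superiority is declared if the lower 95% confidence limit of the odds ratio for pregnancy exceeds 1. The same section announces a comparison of baseline characteristics between the arms but attaches no adjustment to it.

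Under *Selection criteria, Whole cohort*, "women aged 18 to 43 years will be eligible for inclusion in the whole cohort". Under *Study recruitment*, eligibility is checked before randomisation, and the allocation sequence is stratified by centre and by nothing else. Under *Experimental design*, "Four centres in Paris and its suburb area with various socioeconomic contexts will participate".

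The sample size rests on a comparison of two proportions. The effect among couples who take up the programme is "from 20 to 32% in absolute values, respectively". It is assumed that "refusal of PEPCI experimental care would intervene for 20% of subjects", so the difference "according to the intention-to-treat principle, would therefore be 20% versus 29.6" per cent.

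**The concern.** Female age is known for every couple at the eligibility check, spans 25 years and is a plausible predictor of pregnancy. Leaving it out of both the stratification and the primary model has two consequences. Some precision is forgone, because a logistic model that includes a prognostic covariate tests the arm effect with somewhat more power. And if the arms happen to differ in age, the difference stays in the primary estimate, while any adjustment chosen after the baseline comparison would be post hoc.

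This is not a detail the article leaves to the statistical analysis plan. It states the terms of the primary model and the decision rule explicitly.

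**Working it through.** **Step 1: the plan's own sample size.** Inputs from *Sample size and statistical analysis*: "Given a two-sided alpha error of 5%, a power of 80" per cent; 20% versus 32% with take-up; 20% refusal; "a randomisation ratio of 2:1 (control group:experimental group").

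- Diluted rate: 0.8 × 0.32 + 0.2 × 0.20 = 0.296.
- Pooled rate at 2:1: (2 × 0.20 + 0.296)/3 = 0.232.
- Control-arm size, pooled variance, no continuity correction: [1.96 × √(3 × 0.232 × 0.768) + 0.8416 × √(0.20 × 0.80 + 2 × 0.296 × 0.704)]² / 0.096² = (1.433 + 0.639)² / 0.009216 ≈ 466, hence 233 in the experimental arm.

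This matches the stated 466 and 233. Power is 80.0% at 466/233 and 82.6% at the full 500/250. The calculation contains no covariate, so the planned power does not depend on adjusting for age.

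**Step 2: power with and without age.** The documents give no effect of age on pregnancy and no age distribution, so these are assumptions: age normal with mean 34 and SD 5, cut to 18–43; marginal rates held at 20% and 29.6%; 466/233 couples; Wald test from a logistic model. Centre was left out of both models. There were 6,000 simulated trials per scenario (Monte Carlo standard error about 0.5 point).

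| Assumed age effect | Power, arm only | Power, arm + age | Sample-size equivalent of the gain | Age-conditional OR |
|---|---|---|---|---|
| none | 80.2% | 80.2% | 0% | 1.68 |
| OR 0.95 per year | 80.2% | 80.5% | 0.8% | 1.69 |
| OR 0.92 per year | 80.4% | 81.8% | 2.7% | 1.71 |
| OR 0.90 per year | 80.5% | 82.2% | 3.8% | 1.72 |
| OR 0.85 per year | 79.3% | 82.7% | 8.4% | 1.78 |
| OR 0.85 per year, only above 35 | 80.0% | 80.5% | 1.0% | 1.69 |

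The gain is about 0 to 3.5 points. The last row fits a straight line in age to an effect that starts at 35.

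**Step 3: chance imbalance.** With 500/250 couples and an assumed SD of 5 years:

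- SE of the difference in mean age: 5 × √(1/500 + 1/250) = 0.387 year. Two SE is 0.77 year.
- Approximate shift in the unadjusted log OR at two SE, as 0.77 × |ln(OR per year)|: at OR 0.92, 0.77 × 0.083 = 0.06; at OR 0.90, 0.77 × 0.105 = 0.08. Over the wider range of 0.95 to 0.85 it runs from 0.77 × 0.051 = 0.04 to 0.77 × 0.163 = 0.13.
- Planned effect: OR = (0.296/0.704)/(0.20/0.80) = 1.68, log OR 0.52. A shift of 0.06 to 0.08 is about 12% to 15% of it.
- Standard error of the unadjusted log OR at 500/250: √[1/(500 × 0.20 × 0.80) + 1/(250 × 0.296 × 0.704)] = √(0.0125 + 0.0192) = 0.178. The shift is thus less than half a standard error.

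**Step 4: what adjustment does to the estimand.** The odds ratio is not collapsible. With the marginal rates fixed at 20% and 29.6%, the marginal OR is 1.68, and the age-conditional OR in the scenarios with an age effect is 1.69 to 1.78 (last column). The marginal risk ratio is 0.296/0.20 = 1.48 and the risk difference 9.6 points; neither changes with adjustment.

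**The case against.** The strongest reply is that nothing in the plan is wrong. The only stratification factor is in the model, the test is valid under randomisation, and the promised power is delivered without age. A two-standard-error imbalance arises in about 5% of trials, and the confidence interval already covers sampling variation of that kind. An unseen analysis plan might also add adjusted sensitivity analyses. All of this stands, and it confines the point to efficiency and robustness. It does not remove the point, because the article fixes the primary model without age.

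A reader might infer more, and the documents do not support it:

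- *That the trial is underpowered or biased.* Step 1 shows otherwise. A larger power gain, to 85–87% at 500/250, appears only if a further strong prognostic score is assumed (log OR 0.5 to 0.8 per SD), and no variable in the documents is shown to be that strong.
- *That a random centre effect with four centres is a fault.* In simulation the centre variance is often estimated at about zero, but the arm estimate barely changes.
- *That an odds ratio overstates the planned effect.* OR 1.68 and RR 1.48 describe the same 20% versus 29.6%. The article uses the OR for its decision rule and does not say that nothing else will be reported.
- *That BMI and duration of infertility should be added as a matter of course.* No recorded duration is listed, only a 12-month threshold. The exclusion limit implies that BMI is known at screening, but the only baseline measurement described is the sports physician's examination, after randomisation and only in couples who accept the programme.

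**Conclusion.** The point holds as a modest improvement. Female age is handled neither by the stratification nor by the primary model, although it is known before randomisation. Adjusting for it would add about 0 to 3.5 points of power for assumed age effects between none and OR 0.85 per year. It would also remove a possible shift of about 0.06 to 0.08 in the log OR under an imbalance of about 0.8 year (at OR 0.92 to 0.90 per year). These sizes rest on an assumed age distribution and assumed age effects; the documents supply neither. If age had no effect on pregnancy in this population, the gain in power would be nil.

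**What to change.** Before outcomes are seen by arm, prespecify female age at inclusion, as a continuous variable, as a fixed covariate in the primary logistic model. Keep arm, the centre term and the decision rule (lower 95% limit of the OR above 1). Add female BMI only if it is recorded before randomisation in both arms.

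State that the reported odds ratio is conditional on age, and give the standardised risk difference and risk ratio from the same model beside it, so that the result can be read against the planned 20% versus 29.6%.

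The cost is a change of wording: no further couples and no new data, since age is needed for eligibility. The one downside is the conditional odds ratio (about 1.69 to 1.78 against 1.68 marginal in the scenarios above), which the standardised measures address.

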#### Ethical, regulatory, and data management considerations

The study protocol has received ethical approvals by the CPP (no. P140934 and no. EUDRACT 2016-AO1281–50 on 22 May 2019). The protocol received authorisation from the ANSM (Agence national de sécurité du medicament et des produits de santé) on 11 February 2016.

The study will be performed in compliance with the Declaration of Helsinki and monitored according to the sponsor’s standard operating procedures. Written informed consent will be retrieved from each participant prior to study enrolment. Data will be recorded on a dedicated e-crf (oneline study notebook) (CleanWEB; Télémédecine Technologies, Boulogne-Billancourt, France). The trial was registered at ClinicalTrials.gov (identifier no. NCT02961907) on 11 November 2016.

The level of monitoring to be set up in this research will be of an intermediate level. The following points will be monitored: (1) existence of included patients, (2) signed informed consent form, (3) eligibility criteria, (4) main criteria, (5) secondary criteria, (6) side effects (e.g., serious side effects, tolerance, new facts), (7) compliance with the monitoring schedule, and (8) data monitoring according to the monitoring guide implemented.

## Discussion

It has been hypothesised that the decrease in male and female fertility could be partially due to environmental and lifestyle factors. Indeed, exposure to pollution, radiation, environmental toxicants, and endocrine disrupters is already known to impact fertility in both males and females [81]. Lifestyle factors such as addictions (tobacco, alcohol, drugs), inadequate diet, lack of physical activity, overweight, obesity, metabolic syndrome, inadequate sleep, and heightened stress levels may also compromise male and female fertility [2, 3, 27, 30, 31, 81]. These lifestyle factors are of interest since they may be reversible and there is a possibility of acting on them.

The PEPCI study has several assets. First, it boasts a holistic approach considering not only inappropriate dietary habits and physical inactivity but also psychological stress, anxiety, and addiction. The intervention is integrated in a global and personalised manner. Importantly, members of couples are involved as partners. Second, not only women but also men are considered. Furthermore, as there are multiple interventions, we will not select only patients with overweight or obesity, as usually is done, but instead individuals with a BMI of less than 49 kg/m^2^.

In addition, an analysis of the effect of a three-month intervention on the targeted factors will allow us to show whether the period of planning pregnancy should be used as a ‘window of opportunity’ to change unhealthy behaviours (M3, second evaluation). Also, with the M12 (at 12 months or when pregnancy is diagnosed) evaluation, we will be able to check whether the effects of the three-month intervention persisted or not.

Fourth, our primary criterion is the clinical ongoing pregnancy rate (i.e. ultrasound determination at 6 weeks of amenorrhea) and not intermediate criteria (according to the pragmatic approach). Usually, ART begins at 3 months after the initial visit and the first 3 months are spent undergoing fertility evaluations. As multidisciplinary interventions are planned during the first 3 months, couples in the intervention group won’t face any additional delay before receiving a first attempt of ART. This was an issue in the study by Mutsaert et al. because women assigned to the lifestyle intervention had access to infertility treatment 6 months later than those in the control group, which induced a lower rate of pregnancies in the follow-up window [19].

Fifth, this controlled trial was conceived as a pragmatic way to investigate the effectiveness of a complex medical intervention under usual conditions. For this purpose, we used the ‘cohort multiple randomised controlled trial’ methodology, with prerandomisation, as accepted by the National Health Service research ethics committee [57] and the French ethics committee to strengthen the external validity by limiting selection bias and recruitment difficulties that may result from initial consent to randomisation. Moreover, for pragmatic trials with a usual care comparator that is available outside the trial, the only incentive to participate is to receive the new intervention, so patients allocated to treatment as usual may be disappointed and may withdraw from the trial (attrition bias). Lastly, all eligible people are followed within the cohort to obtain realistic estimates of adherence, benefits and adverse events, if any exist. One of the limitations of this study is that full blinding will not be possible; however, the main criteria will be assessed blindly. With this methodology, blinding for patients in the control group will be preserved.

The weakness of this study is the absence of a pilot study that would anticipate its feasibility. In addition, there is no conceptual model of the intervention established, although we determined the nutritional program to be applied according to the available literature at the time of study conception. Furthermore, for economic reasons, we had to opt for a 2:1 design. There are also limitations with deploying an intervention via an Internet platform since there are equipment constraints. Finally, the multidisciplinary approach and the possibility for the patient to choose the intervention allows for tailor-made patient care but it makes it difficult to explain the factors that might have actually influenced the birth.

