## Objectives and outcomes

The main objective of this randomised study is to demonstrate that periconceptional multidisciplinary care aiming to evaluate and optimise habits of infertile couples (i.e., diet and lifestyle factors) has a positive impact on reproductive functions as a whole, including birth issues, relative to a routine approach. We will also focus on feasibility, acceptance, compliance, and conditions of success of a multifaceted lifestyle intervention.

The primary outcome of this trial is the rate of clinical ongoing pregnancies (ultrasound determination of a gestational sac at 6 weeks of amenorrhea), either after the first ART attempt performed within three to 12 months of the initial visit or during a spontaneous pregnancy occurring within 12 months after the initial visit. Couples who do not conceive during the study period (within 12 months of the initial visit) will be considered as failures. Ultrasound performed at 6 weeks of amenorrhea will be performed by an operator blinded to the intervention arm.

The secondary outcomes will allow us to compare the two arms of the trial regarding (1) the couple’s adherence, satisfaction with the program, and understanding of the importance of receiving care; (2) changes in risk factors (e.g., nutrition, addiction, physical activity, psychological factors); (3) evolution of metabolic biomarkers (including folic acid); (5) sperm quality evolution (conventional semen parameters and DNA integrity); (5) TTP; and (6) quality of life. In cases of ART, we will assess outcomes including fertilisation rate, top quality embryo rate, implantation rate, and the number of ART procedure attempts needed to achieve pregnancy within 12 months.

The tertiary outcomes concern a subgroup of pregnant women followed until delivery, through evaluation of (1) maternal complications and pregnancy outcomes (e.g., prematurity, pregnancy living), (2) newborn check-up results, (3) quality of breast milk, and (4) further analyses of collected cord blood.

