#### Patients involved in the controlled trial (Figs. 2 and 3)

All couples recruited in this trial will be assessed at baseline (M0), while the couples who accepted to undergo the PEPCI intervention will be evaluated 3 months later (M3). Then, all couples (control and experimental arms) will be followed for 12 months (M12) or evaluated at the time of pregnancy diagnosis and then until delivery.

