The sports physician will perform an interrogation (e.g., a familial history of obesity, diabetes, or cardiovascular diseases and personal history of metabolic, endocrinologic, and cardiovascular diseases); a physical examination (i.e., blood pressure, heart rate, BMI, and waist and hip circumferences); a cardiovascular (rest electrocardiogram), rheumatologic, and endocrinologic examination if needed; and a body composition assessment (single-frequency bioelectrical impedance analysis at 50 kHz using the Tanita BC 420 S MA from Tanita Corp., Tokyo, Japan) [71]. The physician also will evaluate physical activity levels through the self-assessed IPAQ questionnaire filled upstream on the web platform.The dietician will evaluate diet and eating habits, individual tastes, and abilities. Interrogation is partly based on the results of the Binge eating Scale and a self-reported food frequency questionnaire filled on the web platform. The dietician verifies the responses to the food frequency questionnaire with the patients (e.g., for declared quantities).The psychiatrist will screen the participants for depression and anxiety using the self-reported HAD questionnaire. Both members of the couple will undergo a structured clinical interview based on (1) the Miniature International Neuropsychiatric Interview (MINI 5.0) [72] for the diagnosis of psychiatric conditions according to the *Diagnostic and Statistical Manual of Mental Disorders*, fourth edition and (2) on the Alcohol, Smoking and Substance Involvement Screening Test for the screening of substance use disorders.

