#### Data collection and assays 3 months after M0 in the intervention group (M3)

Couples included and who have consented to the initial PEPCI intervention (experimental arm) will complete a second consultation with the same sports physician, dietician, and psychiatrist, undergoing the same evaluations as included in M0 (i.e., questionnaires and sample collections).

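### The M3 evaluation covers only couples who accepted PEPCI, so it cannot show a three-month effect on lifestyle factors; the randomised comparison exists only at M12 or pregnancy diagnosis

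*Protocol article*

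**What the plan says.** **The claim.** The Discussion ties its promise to the second evaluation at M3: "an analysis of the effect of a three-month intervention on the targeted factors will allow us to show" whether this period should be used to change unhealthy behaviour. It adds that, with M12, "we will be able to check whether the effects of the three-month intervention persisted or not".

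**Who is seen at M3.** The section on M3 data collection reads: "Couples included and who have consented to the initial PEPCI intervention (experimental arm) will complete a second consultation". The section on patients in the controlled trial says the same: M3 is for couples who accepted, and both arms meet again only at M12 or at pregnancy diagnosis.

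**Two-arm outcomes.** Objectives and outcomes states: "The secondary outcomes will allow us to compare the two arms of the trial". The list includes adherence, satisfaction with the programme, and changes in risk factors, with addiction named among them. The statistical section plans mixed regression models for the effect of the intervention on such criteria, and names adherence and satisfaction.

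**Measures given to accepters only.** The M0 section reserves the detailed evaluation for couples who agreed to the intervention. It contains "the Alcohol, Smoking and Substance Involvement Screening Test for the screening of substance use disorders" (ASSIST), and in it "The dietician verifies the responses to the food frequency questionnaire with the patients". The questionnaires listed for the whole cohort cover diet, binge eating, physical activity, sleep, anxiety and depression, quality of life and locus of control. No tobacco, alcohol or drug instrument is named.

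**The concern.** To speak of an effect of the programme at three months, one needs to know what would have happened over those months without it. Controls and refusers would supply that information, and neither has an M3 visit. Accepters may be more motivated than the rest. All couples are also in fertility work-up during these months, which may itself change habits. In addition, each couple's objectives are set from the M0 assessments, so factors that looked poor on that day are likely to be the ones pursued, and some of them would look better on re-measurement in any case.

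The persistence claim inherits the problem: M12 cannot show whether an effect lasted if the effect was never estimated. The article's closing section hopes for public recommendations on periconceptional habits, and a favourable M3 change could be read as trial evidence for them. For addiction, and for programme adherence and satisfaction, a two-arm comparison is announced but the measures described do not provide one.

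**Working it through.** **1. The plan's own figures** (Sample size and statistical analysis). With 20% refusal, the diluted rate in the experimental arm is 0.8 × 0.32 + 0.2 × 0.20 = 0.256 + 0.040 = 0.296, the stated 29.6%. The stated 466 and 233 couples also reproduce (two-sided 5%, 80% power, 2:1, pooled variance, no continuity correction). 699 / 0.95 = 736, so 750 covers the 5% dropout. None of this is in dispute; it supplies the acceptance fraction.

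**2. Who has M3 data on that assumption.**
- Experimental, accepted: 0.8 × 250 = 200
- Experimental, refused: 0.2 × 250 = 50, none seen at M3
- Control: 500, none seen at M3
- Share of randomised couples: 200 / 750 = 27%

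**3. Measures by time point, as the article describes them.**

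| Measure | M0 | M3 | M12 or pregnancy diagnosis |
|---|---|---|---|
| Common self-questionnaires (SUVIMAX, IPAQ, PSQI, HAD, Duke) | both arms | accepters | both arms |
| Blood and sperm | both arms | accepters | both arms |
| ASSIST | accepters | accepters | not described |
| Dietician-verified food frequency questionnaire | accepters | accepters | not described |
| Programme adherence and satisfaction | no programme in controls | no programme in controls | no programme in controls |

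M12 also includes anthropometrics in both arms. The first two rows support a randomised comparison of change from M0 to M12. No row supports one at M3. M12 falls up to 12 − 3 = 9 months after the programme ends, or earlier at a time that depends on pregnancy, so it does not stand in for a three-month contrast.

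**4. How large regression to the mean could be.** The article gives no test-retest correlation, so this is an illustration on assumed inputs. Let targeted people lie d standard deviations on the unfavourable side at M0, with test-retest correlation r and n people analysed. With no true effect, expected improvement = d(1 − r) SD, approximate standard error = √(2(1 − r)/n), and z is their ratio.

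| d | r | n | Expected change (SD) | SE | z |
|---|---|---|---|---|---|
| 1 | 0.6 | 100 | 0.40 | 0.089 | 4.5 |
| 1 | 0.8 | 100 | 0.20 | 0.063 | 3.2 |
| 1 | 0.6 | 50 | 0.40 | 0.126 | 3.2 |
| 1 | 0.8 | 50 | 0.20 | 0.089 | 2.2 |
| 0.5 | 0.6 | 100 | 0.20 | 0.089 | 2.2 |
| 0.5 | 0.8 | 100 | 0.10 | 0.063 | 1.6 |
| 1 | 0.95 | 100 | 0.05 | 0.032 | 1.6 |

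The artefact ranges from small to clearly significant. If all accepters were analysed on a factor regardless of their M0 value, d would be near 0 and this component would largely vanish. Time trends and self-selection would remain.

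**The case against.** The strongest reply is that the trial does compare risk factors by randomised arm. M12 applies the same self-questionnaires, blood, sperm and anthropometrics to both arms, and a mixed model is named for these outcomes. That stands. A reader might infer that lifestyle change has no control comparison anywhere in the trial; the M12 section rules that out. The gap is the M3 time point and the accepter-only measures.

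Second, a reader might infer that diet is measured with different error in the two arms, so that the two-arm diet comparison is biased or impossible. The article does not support this. It says that the dietician verifies answers, not that corrected values replace the submitted ones. The verified instrument is a food frequency questionnaire used to tailor the intervention, whereas all couples complete the 3-day SUVIMAX. Differential error would arise only if verified data entered the between-arm analysis.

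Third, a reader might call a false positive at M3 near-certain. The last rows of the table above show that this depends on the chosen inputs. The article says objectives are negotiated, not that factors are picked for extreme scores, and some elements are offered regardless of baseline status.

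Fourth, this is a condensed article: the visit-schedule figure is not shown, and the cohort's standardised forms could hold smoking or alcohol items. So the addiction comparison is unsupported by the instruments described, rather than impossible.

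Finally, the M3 claim is a Discussion sentence, and no M3 outcome or M3 analysis is listed elsewhere. That limits the weight of the point. It does not make the sentence correct, because it says what the trial will show.

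**Conclusion.** The point holds in a limited form. The M3 evaluation yields an uncontrolled before-after change in about 200 self-selected couples out of 750 (27%, on the plan's 20% refusal). It cannot show an effect of the three-month programme, and M12 cannot show that such an effect persisted. This follows from the assessment schedule alone and needs no assumption about correlation or selection. Only the size of the likely bias does: on the inputs tried, spurious improvement runs from 0.05 to 0.40 SD.

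Addiction is announced as a two-arm outcome without a two-arm measure being described. Adherence to and satisfaction with the programme cannot be contrasted with a group that has no programme. The primary pregnancy outcome, its intention-to-treat analysis and the sample size are untouched, and the M12 comparison of commonly measured factors is valid in principle. This should be corrected, but it does not threaten the main result.

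**What to change.** **Minimum change, close to costless.**
- Describe the M3 change as a descriptive before-after summary in accepters, and withdraw the effect and persistence claims from the Discussion.
- Base statements about effects on risk factors on the baseline-adjusted intention-to-treat comparison at M12, and report the timing of that assessment by arm because pregnancy brings it forward.
- Report programme adherence and satisfaction within the experimental arm only.
- Use only diet data collected the same way in both arms for between-arm analyses, and state that dietician-verified answers serve tailoring.

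**Addiction.** Give the same self-report tobacco, alcohol and drug items to both arms at M0 and M12, or, if the cohort forms already contain them, name them as the outcome measure. The cost is a few extra questions.

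**Alternative, if a three-month effect is wanted.** Send the M3 web self-questionnaires to all randomised couples, refusers included, and compare arms by intention to treat with baseline adjustment. No extra visit is needed, since questionnaires are already completed on the web platform. The cost is some burden for 500 control couples and possible reactivity: lifestyle questions at three months could prompt change in a usual-care arm that the Discussion wants kept blind, and could dilute the pregnancy contrast. This route controls only the questionnaire factors; changes in blood and sperm at M3 would remain descriptive.
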